### Primary and secondary outcomes

The registered primary outcomes at clinical trials.gov for both managers and employees are perceived self-care and staff-care (see Fig. 2) as well as perceived stress, burnout, job satisfaction and sickness absence.

The registered secondary outcomes for both managers and employees are well-being, the overall perception of the psychosocial work environment as well as turnover intention and, actual turnover.

Additional registered secondary outcomes for only managers was confidence in addressing mental health issues and the psychosocial work environment. For only employees additional secondary outcomes were central aspects of the psychosocial work environment (predictability, role clarity, influence, social support from colleagues and managers, leadership quality, trust between colleagues, demands, and possibilities for solving work tasks), psychological safety and the psychosocial safety climate. Table 1 displays the SPIRIT flow diagram for the schedule of enrollment, intervention and assessment. Specification of measures and data collection is provided below.

**Table 1 Tab1:**
[figure not shown]
SPIRIT flow diagram of the schedule of enrollment, intervention and assessment of the study

### Data collection (effect evaluation)

The participating managers randomly allocated to the intervention and waitlist control group and all their employees, will be invited to complete questionnaires at baseline, 6 months follow-up and 6-months post training (12 months follow-up). Register data on sickness absence and staff turnover will be retrieved for the one year period prior to and following baseline for all managers and employees. In addition, a process evaluation will be conducted including both quantitative and qualitative data (see description below).

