## Methods

### Study design and participants

The project will investigate the effects of training frontline managers in hospitals in the Central Denmark Region through a cluster randomized waitlist controlled trial. The project aims to include 200 managers who, after registration and informed consent for the research project, are randomly allocated to receive either leadership training commencing in the beginning of 2023 (intervention group), or leadership training commencing in the beginning of 2024 (waitlist control group). Recruitment began in May 2022 and ended during January 2023. The participating managers are randomized by hospital ward, but the vast majority of wards include only one participating manager. Because some managers are clustered in wards, the wards are stratified into three groups of wards with: 1. One participating manager in the ward, 2. two participating managers, and 3. three or four participating managers. In each strata, wards are randomly assigned to equal sized intervention and control groups. For each strata, we randomly number all wards and using the RAND function in Excel, each ward is assigned with a random number between 0 and 1. The lowest 50% of numbers are assigned to the intervention group and the other 50% are assigned to the control group. In addition, the intervention group is randomly assigned to five training groups. The randomization is conducted by a neutral research assistant. All managers and their employees will be invited to complete outcome questionnaires at baseline prior to training, as well as 6-months and 12-months post baseline. An overview is presented in the flowchart in Fig. 1. Managers will also receive a short questionnaire related to the process evaluation following completion of each training module to assess the learning experience (see further description of the process evaluation below).

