#### Consent

For the participating managers and their employees, active informed consent was a prerequisite in order to participate in the study. The participating managers gave their informed consent, when they signed up for the study, while employees will provide their informed consent prior to completing the baseline questionnaires.

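### As worded, wards are allocated before the baseline questionnaire and employee consent, and nothing shown keeps the arm hidden until baseline closes

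*Protocol article*

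**What the plan says.** Four places in the protocol article bear on the order of events.

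- Study design and participants: the project recruits managers "who, after registration and informed consent for the research project, are randomly allocated to receive either leadership training". No baseline measurement is mentioned between consent and allocation. The unit of randomisation is the ward.
- The same section says that managers and employees are "invited to complete outcome questionnaires at baseline prior to training". This ties baseline to the training, not to the allocation or its disclosure.
- The section on data collection for the effect evaluation describes the baseline invitees as people who already have an arm: "The participating managers randomly allocated to the intervention and waitlist control group and all their employees, will be invited to complete questionnaires at baseline".
- Consent: managers consented at sign-up, whereas "employees will provide their informed consent prior to completing the baseline questionnaires". Employee entry is therefore a separate and later step.

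Statistical analyses defines the effect by three between-group differences in mean change: T0-T1, T0-T2 and T1-T2. The model has time, group and their interaction as fixed effects. The only blinding stated is that of the data analyst. The randomisation is done by a neutral research assistant.

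**The concern.** Most of the registered primary outcomes are self-reports: self-care, staff-care, stress, burnout and job satisfaction. The arms are easy to tell apart, because one starts training at once and the other waits more than 12 months. A manager who knows the arm when filling in T0 may answer differently because of it. Randomisation cannot remove such a difference, since it arises after allocation. T0 is one half of two of the three effect quantities.

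Employees are a second, separate route. If they decide whether to consent after their manager's arm is known, the consenting sample can differ between arms even though the wards were randomised. That is the usual recruitment bias of cluster trials. It would carry into all three employee-level questionnaire contrasts, including T1-T2.

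**Working it through.** **Order of events.** Set side by side, the statements run: manager consent, allocation, invitation of allocated managers and their employees to T0, employee consent at T0, training. No statement puts T0 or employee consent before allocation.

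The dates leave little slack. "Recruitment began in May 2022 and ended during January 2023", and training starts at the beginning of 2023. Register data run from January 2022 to January 2024 with one year on each side of baseline, which puts baseline near January 2023. The T0 response window is at least three weeks. Allocation, notice of training dates and T0 therefore fall close together.

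**The plan's own power figure.** Inputs from Sample size: effect 0.54, baseline correlation 0.5, group size 20, intra-group correlation 0.02, 80 managers per arm followed up, alpha 0.05 (two-sided assumed).

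- Design effect: 1 + (20 − 1) × 0.02 = 1.38.
- Change-score variance in SD² units: 2 × (1 − 0.5) = 1.
- Standard error: √(2 × 1 × 1.38 / 80) = 0.186.
- Power: Φ(0.54/0.186 − 1.96) = 0.828, which matches the stated 0.83.

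With T0 as a covariate (variance 1 − 0.5² = 0.75) power would be 0.919, which does not match. The stated figure thus fits an unadjusted change contrast, as does the planned group-by-time model.

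**Bias from a T0 shift.** Let s be the arm difference in T0 self-reports caused by knowing the arm, and p the part of it still present at follow-up.

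- Change from T0: bias = p − s. If the shift is gone by follow-up (p = 0), its size is s. If it persists in full (p = s), it cancels.
- T0 as covariate with correlation 0.5: bias = p − 0.5s, so half of s when p = 0.
- Follow-up comparison without T0: bias = p.
- T1-T2: the T0 value does not enter.

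The documents give no value for s. Assuming 0.1 to 0.2 SD, wholly transient (p = 0):

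| s | Bias, change contrast | Share of 0.54 | Type I error | Power if against effect | Power if in favour | Bias, T0 covariate |
|---|---|---|---|---|---|---|
| 0.10 | 0.10 | 18.5% | 0.084 | 0.659 | 0.931 | 0.05 (9.3%) |
| 0.20 | 0.20 | 37.0% | 0.190 | 0.448 | 0.979 | 0.10 (18.5%) |

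The type I error and power columns are for the change contrast. With s = 0 they are 0.05 and 0.828.

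The direction is not known either. Optimism in the training arm or disappointment in the waitlist arm at T0, if it fades, works against the effect; the reverse works in its favour. The power figures apply to managers, whom the sample-size section counts.

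**Employee selection.** The documents give no consent or response rates, so no size can be put on this.

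**The case against.** The strongest reply is that the order is inferred. The words about allocation in the data-collection section may merely describe who the participants are, since that sentence covers all three time points. A baseline that precedes training fits either order. Fig. 1 (flowchart) and Table 1 (SPIRIT schedule) would show the sequence and are not shown, and a journal article condenses the full protocol. Even if the draw came first, bias needs disclosure before T0, and no section says when managers or employees were told. This stands: a reader might infer that T0 was demonstrably answered with knowledge of the arm, and the text does not establish that.

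Other parts also stand.

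- A reader might infer that every change contrast is biased through T0. T1-T2 does not use T0.
- A reader might infer that a T0 shift always passes through in full. A persistent reporting shift cancels in a change score.
- A reader might infer that the employee groups are non-comparable. The text supports only a risk. All employees under direct staff responsibility are included, they are identified from HR hierarchies, managers only validate a supplied list, and non-responders get three reminders.

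What does not stand is that the matter can wait for the analysis plan. The order of consent, baseline and allocation is a design fact. Each statement on it in the article is compatible with the exposed order, and the most natural reading points to it.

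**Conclusion.** The point holds in conditional form. The article's wording puts allocation of wards after manager consent and before T0 and employee consent, and nothing shown protects either from knowledge of the arm.

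If the arm was known by then, T0-T1 and T0-T2 for the questionnaire outcomes are biased to the extent that the shift has gone by follow-up. All employee-level questionnaire contrasts are open to selection by arm. Pre-baseline register sickness absence values are not affected by knowledge of the arm.

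The size is unknown. The range of 19% to 37% of the planned effect rests on an assumed, wholly transient shift of 0.1 to 0.2 SD in an unadjusted change contrast. The stated power and sample size are not in error. This is a cheap improvement to the design, not proof of a biased trial.

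**What to change.** State the order of employee listing, employee consent, T0, randomisation and disclosure, and when managers and employees learned their arm.

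Where the order can still be set, complete the employee list, employee consent and the T0 questionnaire, and close T0, before wards are randomised or the allocation is disclosed. If wards must be drawn earlier for planning, the neutral research assistant holds the list until T0 closes. This needs no extra participants or visits. Its cost is that managers learn their training dates about three weeks later, the length of the T0 response window.

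Recruitment had ended before the article was published in May 2023, so T0 may already have been collected. If it was collected after disclosure:

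- Report employee consent and T0 response by arm. This is the only item here that speaks to employee selection.
- Report T0 response dates relative to the date of disclosure.
- As a sensitivity analysis only, compare the arms at T1 and T2 without the T0 questionnaire value, adjusting for variables fixed before allocation: age, gender, occupation and prior register sickness absence. Say plainly that this guards against a transient T0 shift and removes neither a persistent reporting shift nor employee selection.

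The cost of this fallback is a dated statement, a table by arm and one extra analysis.

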#### Quantitative assessment

The quantitative assessment encompasses both questionnaire data and register data on participating managers and their employees.

#### Questionnaires

The three questionnaires are sent out to the participating managers and their employees at three points in time (baseline, 6 months follow-up and 12-months follow-up).

#### Single items

##### Sociodemographic data

The participating managers and their employees will be asked to provide their gender, age, marital status, children living in the household, and highest educational level attained.

##### Work-related data

Regarding their current employment, we ask the managers about their managerial experience (years), their average number of working hours, and whether they have received leadership training prior to signing up for this program. Through HR-data, we were able to assess span of control (the number of employees for whom each manager is responsible), job titles, and which professions their employees represent. Furthermore, the managers are asked about their general job satisfaction [43] and turnover intention. The employees were asked about their average working hours, job satisfaction, the overall perceived psychosocial work environment [43], and their turnover intention. We also asked employees to assess a question we developed on the perceived quality of their care when in contact with patients.

##### Health-related data

Both participating managers and their employees were asked to self-report their health status, whether they have been on sick leave due to stress or mental illness during the past 12 months, whether they had been prescribed medication for anxiety or depression, sleeping pills or tranquillizers, and to report on their quality of sleep.

#### Scales

##### Health-oriented leadership

Health-oriented leadership [29] focuses on leadership targeted towards improvement of physical and psychosocial health and has been measured and validated by Franke, Felfe and Pundt [29]. In this study, we use a version adapted to target well-being and mental health, which predominantly focuses on factors relevant for the psychosocial work environment. Health-oriented leadership comprises two dimensions: Self-care (16 items) and staff-care (18 items). A sample item appearing in both scales is “I notice in time, when I need a break”/ “I notice in time, when my employees need a break.” The items are answered on a five-point Likert-scale from “To a very low degree” (1) to “To a very large degree” (5). Self-care and staff-care scales will be administered to both managers and employees.

##### Perceived confidence

This scale measures the extent to which the participating managers feel confident in handling different aspects of the psychosocial work environment [18]. The managers will be asked to state their current level of confidence with the task. A sample item is “Initiating contact with staff on sickness absence leave that you believe might be due to mental illness”. The items are answered on a five-point Likert scale from “Not at all confident” (1) to “Extremely confident (5).

##### Cohen’s Perceived Stress Scale (PSS-10)

The PSS-10 is a 10-item scale [44] measuring the extent to which the participating managers and their employees feel that their life is stressful, unpredictable and uncontrollable on a scale from 0–40. A sample item is “In the last month, how often have you been upset because of something that happened unexpectedly?” Each item is answered on a five-point Likert-scale ranging from “Never” (0) to “Very often” (4).

##### Copenhagen burnout inventory

The Copenhagen Burnout Inventory [27] measures both personal, work-related, and client-related burnout. In this study, we only include the measure of personal burnout – a state of prolonged psychical and psychological exhaustion. The scale goes from 0–20. A sample item is “How often do you feel tired?” Each item is answered on a five-point Likert scale ranging from “Never/almost never” (0) to “Always” (4).

##### WHO well-being (WHO-5)

WHO-5 is a five-item measure [45], uncovering general well-being, by asking respondents to indicate how they have felt for the past two weeks. A sample item is “Over the last few weeks I have felt cheerful and in good spirits”. The items are answered on a six-point Likert-scale ranging from “At no time” (0) to “All the time” (5).

##### Danish Psychosocial Working Environment Questionnaire (DPQ)

The DPQ is a comprehensive tool, focusing on a variety of factors in the psychosocial work environment. The full DPQ consists of 119 items covering 38 different psychosocial work environment dimensions. We include some of the questions, specifically questions on predictability, role clarity, influence, social support from colleagues and managers, leadership quality, trust between colleagues, demands, and possibilities for solving work tasks. The items are answered on a five-point Likert-scale ranging from “Always” (0) to “Never” (5).

##### Psychological safety

We ask both the participating managers and their employees to answer a five-item scale on psychological safety [46], measuring the degree to which people in their workplace feel safe in taking the risk that comes with speaking up and sharing concerns. A sample item is “If you make a mistake in this unit, it is often held against you.” The items are answered on a five-point Likert scale ranging from “Completely disagree” (1) to “Completely agree” (5).

##### Psychosocial Safety Climate (PSC-12)

We adapted six-items from the PSC-12. The PSC-12 measures the extent to which the management protects the mental health and safety of their employees. A sample item is “Management clearly considers the psychological health of employees to be of great importance”. The items are answered on a five-point Likert scale ranging from “Completely disagree” (1) to “Completely agree” (5).

##### Symptom Checklist (SCL-90)

The SCL-90 [47] can help determine the existence psychological symptoms. Nine dimensions can be evaluated. We included the dimensions for depression and anxiety. Participating managers and employees are asked to what extent symptoms has bothered or stressed them during the last week. A sample item is “Nervousness or shakiness inside”. Each items is answered on a five-point Likert scale ranging from “Not at all” (0) to “Extremely” (4).

#### Register data

By utilizing access to social security numbers, we will follow the participating managers and their employees in HR-registers and Statistics Denmark, to unfold how the training affects sickness absence and turnover. These data will be collected starting from January 2022 to January 2024.

Sickness absence outcomes at both manager and employee level will comprise:1) The percentage of sickness absence six months prior to baseline, from baseline to first follow-up and from first follow-up to second follow-up.2) The percentage of sickness absence 12 month prior to baseline and from baseline to second follow-up.

Turnover outcomes at the manager level will comprise:1) Number of managers leaving in each group

Turnover outcomes in relation to employees will comprise:1) For the time periods from six months prior to baseline, from baseline to first follow-up and from first follow-up to second follow-up turnover percentage is estimated as the number of employees, who have left their job, divided by the span of control of the manager.2) Turnover percentage estimated as the number of employees, who have left their job, divided by the span of control of the manager for the time period 12 months before to baseline and from baseline to 12 months after.

#### Collecting the data

The questionnaire data is collected via the online Qualtrics software (Qualtrics, Provo, UT). At each time point, participating managers and their employees will have at least three weeks to complete the questionnaire. During these three weeks, three reminders will be sent out to those who have not yet completed the questionnaire. Register data will be collected retrospectively once the 12 months follow-up period is complete.

#### Sample size

We estimated the number of participants using a power calculation based on survey measures and an expected moderate effect size of 0.54 (consistent with previous studies). We have adjusted for an individual baseline correlation of 0.5 and a group size of 20 with an expected intra-group correlation of 0.02. Participation is voluntary throughout the project and we expect a dropout rate of up to 20%. Based on these assumptions, we anticipate being able to recruit 100 managers per group and successfully to follow up on 80 per group. This would result in a satisfactory power of 0.83 using an alpha value of 0.05.

#### Statistical analyses

To evaluate the intervention effects, we will examine group differences in the measured outcome variables over time. The analyses will consider the clustering of observations of staff within the team of the manager, as well as correlation of the repeated measurements within each staff member. The effect of the intervention will be estimated by three quantities: The difference between groups in mean change from T0 (baseline) to T1 (6-months), T0 to T2 (12-months) and T1 to T2 in the intervention groups versus the control group. Analyses will be conducted as intention to treat and where relevant compared to per protocol analyses. In general, the estimation will be based on a mixed model with time, group and an interaction of group and time as fixed effects. For outcomes measured at manager levels, the mixed model will include a random level for training group, hospital ward and manager. For outcomes measured at the employee level, an additional random level for employee is included. Analyses at the employee level will be further adjusted for employee age, gender, occupation, and span of control of the manager. Possible bias due to missing data will be investigated with a set of sensitivity analyses. Regarding turnover among the managers during the follow-up period, the two groups will be compared by binomial regression corrected for occupation, age, gender. Models will be bootstrapped over ward. The data analyst will be blinded as to who is in the intervention or control group.

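### Estimating effects as differences in mean change, with arm means free at baseline, gives up precision on the T0–T1 and T0–T2 comparisons that baseline adjustment would recover at no cost

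*Protocol article*

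**What the plan says.** Under Statistical analyses, the intervention effect is three quantities: "The difference between groups in mean change from T0 (baseline) to T1 (6-months), T0 to T2 (12-months) and T1 to T2". For estimation, "the estimation will be based on a mixed model with time, group and an interaction of group and time as fixed effects". Manager-level models add random levels for training group, ward and manager, and employee-level models add one for employee. The covariates named are for employee analyses only: age, gender, occupation and the manager's span of control. The baseline value of the outcome is not among them, and no constraint of equal baseline means is stated.

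Under Sample size: "We have adjusted for an individual baseline correlation of 0.5 and a group size of 20 with an expected intra-group correlation of 0.02". The target is to "recruit 100 managers per group and successfully to follow up on 80 per group", with an effect size of 0.54, giving power 0.83 at alpha 0.05. The article does not state whether the test is two-sided or on what scale 0.54 is expressed.

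**The concern.** A model with time, group and their interaction estimates a separate baseline mean for each arm. The interaction is then a change-from-baseline contrast. Randomisation makes the arms' baseline means equal in expectation, so estimating a baseline difference costs precision and carries any chance imbalance into the effect estimate. If r is the correlation between baseline and follow-up, and clustering is ignored, the change contrast has variance proportional to 2(1−r) and a baseline-adjusted contrast 1−r². The second is never larger. At the plan's r = 0.5 they are 1.00 and 0.75.

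At stake is the power of the two comparisons that start from baseline. The margin matters: the plan relies on an effect of 0.54 and 80% retention, and its Discussion names turnover and control managers seeking other training as threats.

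**Working it through.** **Inputs (Sample size):** 80 followed up per arm; d = 0.54; r = 0.5; group size 20; intra-group correlation 0.02; alpha 0.05. **Assumptions:** two-sided test; d in raw outcome standard deviations; total variance 1 at each time apart from clustering; complete data; clustering applied in both arms.

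**Formula.** Write the variance of the difference as 2V/80. Then z = 0.54/√(2V/80), and power = Φ(z − 1.96).

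**The plan's own figure.** Design effect 1 + 19 × 0.02 = 1.38.
- Change contrast: V = 2(1 − 0.5) × 1.38 = 1.38; z = 0.54/√0.0345 = 2.907; power 0.828. The stated 0.83 is reproduced.
- Follow-up only, ignoring baseline: V = 1.38, so again 0.828. The two coincide because 2(1 − 0.5) = 1.

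**Reading A: training-group clustering arises only after T0.**
- Change: V = 1.38 + 1 − 2 × 0.5 = 1.38; power 0.828.
- Adjusted: V = 1.38 − 0.5² = 1.13; z = 3.213; power 0.895.
- The common shortcut of applying the design effect to the whole adjusted variance gives V = 0.75 × 1.38 = 1.035; z = 3.357; power 0.919. This is the upper end of the range; the strict form of this reading gives the lower end.

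**Reading B: clustering is an intercept constant over time,** one way to read a random level for training group. The variance at each time is 1.38 and the covariance between times is 0.5 + 19 × 0.02 = 0.88.
- Change: V = 2(1.38 − 0.88) = 1.00; z = 3.415; power 0.927.
- Constrained baseline: V = 1.38 − 0.88²/1.38 = 0.819; z = 3.774; power 0.965.

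**Size on either reading.** The variance ratio, adjusted to change, is 1.13/1.38 = 0.82 or 1.035/1.38 = 0.75 under A, and 0.819/1.00 = 0.82 under B. That is a reduction of 18% to 25%. To match the adjusted analysis with 80 per arm, the change contrast would need 80/0.819 ≈ 98 to 80/0.75 ≈ 107 per arm.

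**Three time points.** A generalised least squares check, with correlation 0.5 between all pairs of times and before clustering, gives these variance factors:

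| Model | T0–T1 | T0–T2 | T1–T2 |
|---|---|---|---|
| Baseline means free | 1.00 | 1.00 | 1.00 |
| Baseline means equal | 0.75 | 0.75 | 1.00 |

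**Incomplete follow-up.** If the likelihood model also uses all 100 baselines per arm, the unconstrained variance factor is (0.75/80 + 0.25/100) × 80 = 0.95. With the design effect applied in full, V = 0.95 × 1.38 = 1.311 and power is 0.847; adding the clustering term unscaled, V = 0.95 + 0.38 = 1.33 and power is 0.842. Both remain below 0.895.

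**The case against.** The strongest reply is that a group-by-time mixed model is valid and unbiased under randomisation, that the wording is general, and that baseline parameterisation may be settled in an analysis plan not shown. A difference in mean change can also be reported from a constrained model. This stands as a limit on severity. It does not remove the point, because the article goes further than leaving the matter open: it lists a group main effect and names covariates without the baseline outcome.

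Several stronger readings are tempting, and the documents do not support them.

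- *The change contrast gains nothing from baseline.* This is exact only for complete data under Reading A or the full design-effect shortcut. Under Reading B, ignoring T0 gives 0.828 and the change contrast 0.927.
- *Below r = 0.5 the change contrast is always worse than having no baseline.* This also depends on the clustering. At r = 0.4 the shortcut gives 0.756, but Reading B gives V = 2(1 − 0.4) = 1.20 and power 0.877, above the follow-up-only 0.828.
- *The stated 0.83 shows that a change-score analysis was assumed, or is wrong.* A follow-up-only calculation gives the same number at r = 0.5, so 0.83 cannot identify the analysis. Nor is it an error.
- *Precision is lost on every questionnaire outcome.* T1–T2 gains nothing under equal correlations. No employee-level correlation, clustering or power is given, so no employee figure can be computed.
- *Everyone supplies a baseline.* Managers and employees are invited, and participation is voluntary. Entering T0 as an ordinary covariate would drop those without it unless imputed; the planned mixed model keeps them.

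One objection changes the remedy. Managers are randomised after registration and consent, while employees consent just before their baseline questionnaire. The article does not establish that employee T0 precedes knowledge of allocation. If it does not, equal T0 means are not guaranteed, and imposing them could bias the estimate.

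**Conclusion.** The point holds as one of efficiency. For manager questionnaire outcomes at T0–T1 and T0–T2, the model as written has a larger variance than a baseline-adjusted analysis of the same data. Adjustment cuts it by 18% to 25%, worth 0.83 to 0.90–0.92 in power on Reading A and its shortcut, or 0.93 to 0.97 on Reading B. The article does not say which reading applies, so neither pair should be quoted alone. The figures rest on the assumptions listed above. In particular, clustering is applied in both arms, although the article describes training groups for the intervention arm; a design effect there alone gives 0.879 for the change contrast. The issue deserves a change because the remedy uses data already planned, but it threatens neither the validity of the trial nor its stated power.

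**What to change.** Keep the mixed model and its random levels. For each outcome whose T0 value was collected before allocation was known, replace the fixed effects with time and arm-by-post-baseline time, so that T0 means are equal across arms. This form also retains participants with a missing T0. Report the adjusted between-arm differences at T1 and T2.

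Keep the unconstrained change model as a sensitivity analysis for those outcomes. Make it the primary analysis for any outcome whose baseline was answered after allocation was known, notably employee questionnaires if that was the order. State when T0 was collected relative to allocation, separately for managers and employees.

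Restate the power for the analysis chosen, giving sidedness, the scale of 0.54, and whether training-group clustering is taken as constant over time or as arising after T0. The cost is a few sentences in the analysis and sample-size text, with no new participants or data.
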